**Steering Committee Members:**

- [name] – London School of Economics
- [name] – Institute for Clinical Effectiveness and Health Policy
- [name] (Global Leader, Market Access, Roche, representing PCC)
- [name] – Patient advocacy
- [name] – Translational Cancer Genomics / Queen´s University Belfast
- [name] - Professor of Health Economics / University of York
- [name] - Italian Cancer Society
- [name] - Health Technology Assessment / Hospital Clinic Barcelona
- [name] - Institute of Pathology, University Hospital Heidelberg, Germany
- The **collaborative stakeholder group** will be formed by a minimum of 30 participants from European countries (focusing on the EU5 countries, as well as Sweden, the Netherlands, Austria, and Belgium). Participants will be divided into six subgroups based on their roles within the healthcare system. Similar numbers of participants will be recruited from each group to ensure balanced representation. All participants were required to have worked or be currently working in one of the study countries and represent one of the following categories:
  - Patient advocacy /civil society (e.g., ECPC-European Cancer Patient Coalition, Patvocates Research)
  - Decision-makers (e.g., MoH, EU, Procurement, HTAs, Hospital decision-makers)
  - HTA environment/ Regulators (e.g., EMA or notified bodies)
  - Academia (e.g., Bocconi University, Stockholm School of Economics, University of Reims)
  - Industry (e.g., Marivek Healthcare Consulting, MedTech)
  - Physicians (e.g., Italian Cancer Society, Comprehensive Cancer Centre)

Identified individuals will be invited via email, with a formal letter outlining the project's objectives, their expected roles, participation details, and compensation. The invitations will be managed centrally by a single researcher, who is responsible for contacting potential participants via email while copying research managers on the correspondence to ensure proper oversight.

In addition, participants will be allowed to **suggest additional potential members** for the panel. These suggestions will be reviewed by the research team to ensure that new panellists met the necessary criteria and helped maintain balance and representation across stakeholder groups.

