**Step 3: Delphi Round 2 - First Value Judgements**

This round aims to collect participants' value judgements on the importance of each value criteria and value sub-criteria for assessing the value of NGS/CGP diagnostics in Europe.

1. **Value Judgement Process**
   - Participants first will rate each **value criteria** on a **Likert scale** ranging from 1 to 5, where 1 represented "not at all important," 2 "low importance," 3 "moderate importance," 4 "important," and 5 "very important." Following this, value sub-criteria will be presented in **separate sections** corresponding to each value criteria on the web platform, and participants will then be asked to assess each sub-criteria using the same scale.
   - Instruction for this round are as follows:

Value Criteria:

*REQUIRED: Independently score the importance level of each criteria on an ‘importance’ Likert scale, ranging from ‘1: Not at all important’ to ‘5: Very important’.*

*OPTIONAL: You may provide a comment if any aspects are unclear. Please note comments will be used for research context only and will not be used to change sub-criteria for the next round.*

Value subcriteria:

*REQUIRED: Please review each of the following value statements in 8 criteria (Clinical impact; Test performance and quality; Quality of scientific evidence; Non-clinical impact; Impact on health system integration; organisation; and delivery of care; Economic aspects; Ethical, legal and data governance aspects; and Health system priorities) according to their importance within a framework for assessing NGS/CGP technologies for oncology. Please score each statement according to a 5-point importance Likert scale, ranging from ‘1: not at all important’ to ‘5: very important’. Please keep in mind that the purpose of this framework is to act as a decision aid for reimbursement and coverage decisions.*

*OPTIONAL: Please comment on the associated sub-criteria if its wording and/or concepts are unclear. Note: comments will be used for research purposes only and will not impact changes in the framework for the next round.*

1. **Mandatory Judgements**
   - Participants will be required to provide a value judgement for each value criteria and sub-criteria.
2. **Round Duration**
   - This stage of the Delphi process will be kept open for 10-14 days.

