**Stage 4: Statistical Analysis Using Stata**

The objective of this stage is to evaluate the level of agreement across stakeholder groups regarding the importance of NGS/CGP diagnostics in Europe. A series of statistical tests will be applied to analyze participant consistency, agreement, and to identify any significant disagreements between groups. The analyses to be conducted include:

1. **Interrater Agreement (IRA)**: The **Kappa statistic** and **Gwet’s Agreement Coefficient** is employed to measure the extent to which individuals within each stakeholder and country group independently made similar judgments. These metrics assess internal agreement within groups, and groups demonstrating a high degree of internal consistency were compared against one another.
2. **Wilcoxon Test**: This test is used to evaluate the stability of responses within stakeholder groups across Delphi rounds. When significant instability is detected for certain sub-criteria, additional Delphi rounds are considered to achieve consensus.
3. **Interquartile Range (IQR)**: The IQR of the medians is calculated to determine the level of agreement across stakeholder groups. This metric highlights consensus or divergence regarding the importance of specific sub-criteria.
4. **Kruskal-Wallis H Test**: This non-parametric test is used for subgroup analysis to determine whether there are significant disagreements between stakeholder groups on each sub-criteria. Where significant differences are found, **Dunn’s test** is conducted to identify which specific groups disagreed.

Statistical tests will be completed using **STATA 16.1 software** to assess consensus, stability, and median responses across the cohort. Consensus will be evaluated using the **Interquartile Range (IQR)**, with consensus defined as an IQR ≤ 1. The **Wilcoxon test** will be applied to assess the stability of responses between rounds 2 and 3, and between rounds 3 and 4, to determine whether participants changed their opinions over time.

The **inclusion criteria** for the final framework considers both the IQR (≤ 1) and the median response for each sub-criteria. Sub-criteria with a median of "important" or "very important" are classified as **essential** for value assessment, while those with a median of "moderately important" or lower are classified as **complementary** to the assessment process.

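### The median is named as an inclusion criterion but can never exclude an item, so a sub-criterion the panel agrees is unimportant still qualifies as complementary; a median of 3.5 has no class

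*Protocol*

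**What the plan says.** Protocol, Stage 3, Step 3 (Delphi Round 2) defines a five-point scale, "where 1 represented 'not at all important,' 2 'low importance,' 3 'moderate importance,' 4 'important,' and 5 'very important".

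Protocol, Stage 4 sets the consensus threshold, "with consensus defined as an IQR ≤ 1". It then gives the inclusion criteria for the final framework, which use two quantities: the rule "considers both the IQR (≤ 1) and the median response for each sub-criteria". The median enters in two sentences' worth of sorting: "Sub-criteria with a median of 'important' or 'very important' are classified as" essential, "while those with a median of 'moderately important' or lower are classified as" complementary. There is no third class and no minimum median.

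Protocol, Stage 2 says the stakeholder group "will be formed by a minimum of 30 participants from European countries", divided into six subgroups.

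**The concern.** An inclusion rule built on two quantities should let each of them affect inclusion. Here the median affects only the label. An item on which the panel converges at the bottom of the scale satisfies the one condition that can exclude, and then receives a class name under the inclusion criteria.

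The framework is meant to help decision makers with coverage and reimbursement, and this rule produces it. If the gap is noticed only after the ratings are in, someone will have to choose a floor, or place an item with median 3.5, with the results in view. That would be a post hoc decision on the study's main product.

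**Working it through.** The protocol states no figure on this point, so there is none to reproduce. The check applies the written rule to possible rating patterns.

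**Inputs.** Integer ratings 1 to 5 (Stage 3, Step 3). Consensus if IQR ≤ 1; median of 4 or more is essential; median of 3 or less is complementary (Stage 4). At least 30 raters in six subgroups (Stage 2). With n = 30, the quartiles are the 8th and 23rd ordered ratings and the median is the mean of the 15th and 16th.

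**1. Agreement at the bottom of the scale.**
- Thirty ratings of 1: quartiles 1 and 1, IQR = 1 − 1 = 0, median 1. Consensus is met; class complementary.
- Thirty ratings of 2: IQR 0, median 2. Same class.
- The result is the same with 31 raters. It also holds if the IQR is taken over six subgroup medians all equal to 1, since Stage 4 also speaks of an IQR of the medians.

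**2. What can exclude.** Eighteen ratings of 1 and twelve of 3: quartiles 1 and 3, IQR = 3 − 1 = 2, median 1. No consensus. So a low-rated item can fail, but through spread.

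**3. All patterns of 30 ratings.** There are 46,376 possible distributions over the five scale points. Of these, 8,954 + 5,106 = 14,060 have median ≤ 2. The 8,954 fail on IQR; all 5,106 that meet IQR ≤ 1 are complementary. None is excluded because its median is low. These are counts of possible patterns and carry no probabilities.

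**4. The gap between 3 and 4.**
- Fifteen ratings of 3 and fifteen of 4: quartiles 3 and 4, IQR 1, median (3 + 4)/2 = 3.5. Consensus is met; no class applies.
- A more spread pattern (2, 3, 10, 12 and 3 raters giving 1 to 5) also has median 3.5 and IQR 1.
- In the enumeration, 288 distributions of 30 ratings meet consensus and have no class, all with median 3.5. With 31 raters there are none.

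**5. How often the gap could arise.** An unclassified item needs exactly half the ratings at 3 or lower. For n = 30 and independent ratings with probability p of being 3 or lower,

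P = C(30, 15) × p^15 × (1 − p)^15.

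| p (assumed) | P |
|---|---|
| 0.40 | 0.078 |
| 0.45 | 0.124 |
| 0.50 | 0.144 |
| 0.55 | 0.124 |

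The maximum is at p = 0.50. Each value is an upper bound for an unclassified item, because the two middle ratings must also be 3 and 4 and the IQR must be ≤ 1.

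**6. Does another step remove low-rated items?** Step 2 (thematic analysis) removes duplicates and already addressed proposals and merges items, all before any rating. In Step 3, comments are kept for research only and do not alter the items. Steps 4 and 5 let participants revise or confirm ratings. No step after rating drops an item for low importance.

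**The case against.** The strongest defence is that the wording is deliberate. The lower class is explicitly open downwards, Stage 4 gives its objective as evaluating agreement, and no section makes pruning a goal. A two-tier sort of everything agreed on would be coherent, and low-median items could never be labelled essential. That is possible, but the text then should not present the median as an inclusion criterion.

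Nor does the protocol say outright that complementary items are part of the framework; it calls them complementary to the assessment process. That they are included is an inference. It is the natural one, since both classes stand under the inclusion criteria and no excluded class is named.

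Several stronger readings are tempting and are not supported:
- A reader might infer that the rating rounds cannot prune at all. They can, through IQR above 1.
- A reader might call it perverse that an item with median 5 and quartiles 3 and 5 is left out. Withholding inclusion without consensus is what a consensus rule is for.
- A reader might say that items with median 1 or 2 are misclassified. The documents set no standard against which to say so.
- A reader might take 14% as the expected frequency of unclassified items. It needs exactly 30 raters, p = 0.50 and independence. Thirty is a recruitment minimum, non-completers are dropped each round, and participants see earlier responses in Rounds 3 and 4. The final number of raters, its parity and the independence of ratings are all uncertain.

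It is also fair that items drawn from a systematic review and open feedback are unlikely to gather unanimous ratings of 1; that case is an extreme illustration. Assigning half-point medians is a small convention that an analysis plan could settle. The missing floor differs, because the protocol itself states the rule.

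**Conclusion.** The point holds in a limited form. As written, the median labels items and never excludes one, so an item agreed to be of low or no importance meets the rule and is classed as complementary, while only dispersion can keep an item out. This follows from the stated rule and needs no distributional assumption. That such an item then sits in the framework rests on reading both classes as included. How many items would be affected cannot be estimated from the protocol.

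The unassigned median of 3.5 is real but minor: it needs an even number of ratings, and at 30 independent ratings the exact split has probability of at most about 14%, or about 8% at an assumed 0.40.

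Apart from 3.5, the essential class is unaffected and no test is invalidated. It should be fixed, but it does not undermine the study.

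**What to change.** Before the rating rounds, rewrite the rule in Stage 4 so that every combination of IQR and median has one outcome:

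- IQR ≤ 1 and median ≥ 4: essential.
- IQR ≤ 1 and median from 3 to below 4, including 3.5: complementary.
- IQR ≤ 1 and median below 3: not included, reported as agreed low importance.
- IQR > 1: no consensus, reported separately.

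The floor of 3 follows the scale's label of moderate importance. It is a proposal for the sponsor to confirm, and the defect does not depend on it. If the intention is to keep every consensus item, the text should stop calling the median an inclusion criterion and should report low-median items as a class of their own.

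The cost is one paragraph of wording. The downside is that the framework may be shorter.

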**Data Management and GDPR Compliance**

This study will adhere to the General Data Protection Regulation (GDPR) to ensure the privacy and protection of personal data. All personal data collected during the course of this study will be processed and managed in accordance with GDPR guidelines, ensuring the following principles are upheld:

- Lawful, Fair, and Transparent Processing: Personal data will be collected and processed for specified and legitimate purposes. Participants will be fully informed about the nature and scope of the data collection and its intended use.
- Data Minimization: Only data that is strictly necessary for the research purposes will be collected and retained.
- Consent: In compliance with GDPR, informed consent will be obtained from all participants prior to data collection. Participants will be informed of their rights, including the right to withdraw from the study at any time without any adverse consequences.
- Data Security: Appropriate measures will be taken to safeguard all personal data, including secure storage, and controlled access.
- Anonymization: Where possible, data will be anonymized to protect the identities of participants. Identifiable information will be separated from research data, and all analysis will be conducted on de-identified datasets.
- Data Breach Policy: In the event of any data breach, participants will be promptly notified, and the relevant authorities will be informed, in accordance with GDPR's breach notification requirements.

This study will seek ethics approval, and all data handling protocols will be reviewed and deemed compliant with GDPR requirements.
